**PURPOSE:**

The present study is part of a clinical development programme of Artekin which includes another phase III study to be conducted in Africa.

The proposed amendment has been formulated in response to specific recommendations of the Data Monitoring Committee (DMC) of the study, as described in the minutes of the first meeting of this Committee.

- The DMC made the recommendation that the Sponsor should harmonize the statistical approach for the African and the Asian studies.
- The DMC raised some concern about the second primary endpoint ‘the cure rate of Artekin must be at least 90%’.

According to these recommendations, the following changes are proposed:

- re-formulation of the primary objective;
- inclusion of a new patient population, i.e. the modified intention-to-treat population;
- inclusion of an interim analysis for the sample size re-assessment.

Other changes proposed in the present amendment are minor corrections of the protocol, and the notification that, in addition to the Steering Committee and the DMC, a third Committee (i.e. the Clinical Development Committee) has been constituted with the responsibility of evaluating the recommendations made by the other Committees and possibly transforming them in final decisions.

**MODIFICATION:**

**Page 5: Synopsis Countries**

**Reason for modification:** China will no longer be participating in the study

*Therefore:*

3 countries: Thailand, China and Laos.

*is modified as follows :*

2 countries: Thailand, and Laos

**MODIFICATION:**

**Page 5: Synopsis Study Centers**

**Reason for modification:** China will no longer be participating in the study and the number of sites has increased in Laos

*Therefore:*

8 sites in Thailand, 1 site in China and 1 in Laos

*is modified as follows :*

8 sites in Thailand and 2 in Laos

**MODIFICATION:**

**Page 5: Synopsis Methodology**

**Reason for modification:** There is no stratification in the study. The synopsis reflects an old version of the protocol

*Therefore:*

A phase III, randomized, open label, two arms study.  
Randomization will stratify infants, children and adults by age.

*is modified as follows :*

A phase III, randomized, open label, two arms study.

**MODIFICATION:**

**Page 5: Synopsis Objective (Primary objective)**

**Reason for modification:** This change has been proposed to reflect the new formulation of the primary objective (see below).

*Therefore:*

The primary objective of the study is to measure the Day 63, PCR corrected cure rates of Artekin and AS+MQ and demonstrate that:

- the cure rate of Artekin is non-inferior to that of AS+MQ (non-inferiority margin = 5%);
- the cure rate of Artekin is at least 90%.

This cure rate is defined as the proportion of patients with adequate clinical and parasitological response at Day 63 plus those treatment failures identified as new infection by PCR.

*is modified as follows :*

The primary objective of the study is to measure the Day 63, PCR corrected cure rates of Artekin and AS+MQ and demonstrate that the cure rate of Artekin is non-inferior to that of AS+MQ (non-inferiority margin = 5%). This cure rate is defined as the proportion of patients with adequate clinical and parasitological response at Day 63 plus those treatment failures identified as new infection by PCR.

In order to compare the study results with the historical ones, the criteria described in the WHO document (“Assessment and Monitoring of Antimalarial Drug Efficacy for the Treatment of Uncomplicated Falciparum Malaria – 2003”. See chapter 7, section 7.3) will be used.

**MODIFICATION:**

**Page 18: Section 2.1 – Primary objective**

**Reason for modification:** This change reflects the need to clearly distinguish the two objectives of proving non-inferiority on one side and comparing the study results with the historical ones on the other side. It also clarifies some aspects of the historical comparisons. The requirement of a cure rate higher than a pre-specified threshold for only one of the two treatments under comparison was in contradiction with the comparative nature of the trial. Suppose that at the end of the study the two cure rates were 85% and 87% for the AS+MQ and the Artekin groups, respectively. What could the conclusion be from the study according to the old formulation of the primary objective?

As declared in the WHO document described above, the cure rate threshold is intended for judging the results of single arm studies, aimed at the development of malaria policies, but not at interpreting results of comparative studies.

Of course, in non-inferiority studies there is the problem of showing the external validity of the trial: in fact, the equivalence (or non-inferiority) of the treatments under comparison could be theoretically shown at a level of non efficacy (see ICH guideline E10). To this extent, the comparison of the study results with historical data is very important. However, this comparison should involve both treatment groups.

Furthermore, the potential “confounding” factors that could impact the interpretation of results from trials with concurrent randomized arms are different from the ones that can

impact the interpretation of historical comparisons: in the former case the primary focus is on bias and variability, while in the latter it is on reproducibility of the experimental setting; in the former case the decision rule is of a black or white nature while in the second the efficacy threshold has the role of a “rule of thumb” (see WHO document). Therefore, the statistical techniques suited for the two analyses are different (see statistical section below).

For these reasons, the two objectives of showing non-inferiority of Artekin vs AS+MQ on one side and comparing the study results with the historical ones on the other side have been described as two separate and well distinguished objectives.

*Therefore:*

The primary objective of the study is to measure the Day 63, PCR corrected cure rates of Artekin and AS+MQ and demonstrate that:

- the cure rate of Artekin is non-inferior to that of AS+MQ (non-inferiority margin = 5%);
- the cure rate of Artekin is at least 90%.

This cure rate is defined as the proportion of patients with adequate clinical and parasitological response at Day 63.

*is modified as follows :*

The primary objective of the study is to measure the Day 63, PCR corrected cure rates of Artekin and AS+MQ and demonstrate that the cure rate of the former treatment is non-inferior to that of the latter (non-inferiority margin = 5%). This cure rate is defined as the proportion of patients with adequate clinical and parasitological response at Day 63 plus those treatment failures identified as new infection by PCR.

In order to compare the study results with the historical ones, the criteria described in the WHO document (“Assessment and Monitoring of Antimalarial Drug Efficacy for the Treatment of Uncomplicated Falciparum Malaria – 2003”. See chapter 7, section 7.3) will be used, i.e. the failure rates computed in each treatment group individually considered will be judged against the efficacy threshold of 90%.

#### **MODIFICATION:**

##### **Page 20: Section 3.4 – Sample size**

**Reason for modification:** The rewording of the first section reflects the new formulation of the primary objective. The inclusion of the interim analysis for sample size re-assessment reflects the need of verifying the assumptions on which the sample size computation has been based, given the high impact on the final figures that even small changes in the assumptions can have and the limitation of the available data.

*Therefore:*

The study is designed as a non-inferiority trial.

The level of the PCR-corrected cure rate at day 63 for Artesunate+Mefloquine has been estimated, through a literature search, to be in the range 92%-95%.

The opinion of physicians and experts in malaria treatment has been sought for defining the non-inferiority margin, and this has been set at 5%. In addition, the experts have agreed that,

in order for the new treatment to be considered efficacious in Asia, its PCR-corrected cure rate at day 63 should not be lower than 90%. Therefore, in the present trial, DHA+PPQ will be considered efficacious if both the following conditions are met (see section 2.1):

- (i) the PCR-corrected cure rate at day 63 of DHA+PPQ is not inferior to the cure rate of AS+MQ by 5% or more, and independently of the reference drug performance,
- (ii) the cure rate of DHA+PPQ is at least 90%.

In summary, for the non-inferiority analysis, the clinical and statistical specifications for the sample size computations are as follows:

- Primary endpoint = PCR-corrected cure rate at day 63.
- Primary analysis = based on 97.5% one-sided confidence intervals for the difference in cure rates.
- Alpha = 0.025 (one-sided).
- Power = 80%.
- Cure rate of Artesunate+Mefloquine = at least 92%.
- Non-inferiority margin for the difference (test-reference) = -0.05.
- Randomization: based on a 2 :1 allocation scheme (test : reference).
- Rate of patient attrition in the Evaluable Population (i.e. rate of withdrawals and protocol violations) = 15%.
- Primary Analysis Populations = both the Intention To Treat (ITT) and the Evaluable Populations.

A simulation was performed for estimating the overall power that this study would have for addressing both of its primary objectives. That power was computed for both the lower bound of a 97.5 one-sided confidence interval for the treatment difference being above -0.05 and the point estimate for the test treatment being at least 90%. The scenario in which both treatments have cure rates of 90% has the contra-indicating limitation of a power of 50% for the point estimate for the test treatment to exceed 0.90, no matter how large the sample size is (in fact, if the true success rate is 90% for the test treatment, then 50% of studies will have an observed success rate > 90% and 50% of studies will have an observed success rate < 90%). Thus, one inherently needs to make the assumption that both cure rates are at least 91% in order to identify a realistic sample size with acceptable power.

Details on the above mentioned simulation are provided in a separate document (see Sample Size and Design Justification for The Pivotal Clinical Trials of Dihydroartemisinin+Piperaquine).

Based on the above assumptions, the recommended sample size is 350 in the Artesunate+Mefloquine arm and 700 in the Dihydroartemisinin+Piperaquine arm (1050 patients in total).

The sample size of 1050 patients will concern the ITT population. For both the test and the reference compounds, the cure rates are expected to be higher in the Evaluable population as compared to the ITT population. Therefore, even if the Evaluable population is smaller than the ITT population, no impact on sample size is expected.

An unequal randomization with 2:1 structure was chosen because it assures a larger sample size for the DHA+PPQ group which provides the following advantages:

- a more precise estimate of the DHA+PPQ cure rate;
- a bigger sample for the integrated safety data base of DHA+PPQ, that renders more likely the elucidation of rare adverse reactions, if any.

From an ethical point of view, this choice appears reasonable in view of the previous data on DHA+PPQ, in terms of both safety and efficacy

*is modified as follows:*

### 3.4.1 Sample Size Computation

The study is designed as a non-inferiority trial.

The level of the PCR-corrected cure rate at day 63 for Artesunate+Mefloquine has been estimated, through a literature search, to be in the range 92%-95% in the Intention-To-Treat (ITT) population. The opinion of physicians and experts in malaria treatment has been sought for defining the non-inferiority margin, and this has been set at 5%.

An unequal randomization with 2:1 structure was chosen because it assures a larger sample size for the DHA+PPQ group which provides the following advantages:

- a more precise estimate of the DHA+PPQ cure rate;
- a bigger sample for the integrated safety data base of DHA+PPQ, that renders more likely the elucidation of rare adverse reactions, if any.

From an ethical point of view, this choice appears reasonable in view of the previous data on DHA+PPQ, in terms of both safety and efficacy.

Sample size was initially (see original version of the protocol) computed considering the original formulation of the primary objective, which required the use of a simulation (details are provided in a separate document - see Sample Size and Design Justification for The Pivotal Clinical Trials of Dihydroartemisinin+ Piperaquine).

Having divided the two criteria of non-inferiority and comparison of study results with historical ones, power has been recomputed for each of the two objectives as described below.

For the non-inferiority analysis, the clinical and statistical specifications for the sample size computations are as follows:

- Primary endpoint = PCR-corrected cure rate at day 63.
- Primary analysis = based on 97.5% one-sided confidence intervals for the difference in cure rates.
- Alpha = 0.025 (one-sided).
- Power = 80%.
- Cure rate of Artesunate+Mefloquine in the pure ITT population = at least 92%.
- Non-inferiority margin for the difference (test-reference) = -0.05.
- Randomization: based on a 2 :1 allocation scheme (test : reference).
- Rate of patient attrition in the modified intention-to-treat population as compared to the pure ITT population (i.e. rate of non-informative withdrawals, i.e. reason number 7 of section 5) = 5%. Expected 63-day PCR corrected cure rate in this population = 93%.
- Rate of patient attrition in the Per Protocol Population as compared to the ITT population (i.e. rate of withdrawals for any reason and protocol violations) = 20%. Expected 63-day PCR corrected cure rate in this population = 95%.
- Primary Analysis Populations = both the modified Intention To Treat (ITT) and the Per Protocol Populations.

With these assumptions, the sample size of 1050 patients (700 in the Artekin group and 350 in the AS+MQ group) provides a power of approximately 80% for the lower bound of a 97.5 one-sided confidence interval for the treatment difference being above -0.05 in the modified ITT and 84% for the same analysis in the Per Protocol population (for the power calculation both continuity correction and inequality of variances under the null hypotheses have been considered).

For the historical comparisons, the clinical and statistical specifications for the sample size computations are as follows:

- Anticipated population proportion of clinical failures = as high as 10%.
- Confidence level = 95% (two-sided interval).
- Precision = 5 percentage points.
- Rate of patient attrition in the Per Protocol Population as compared to the ITT population (i.e. rate of withdrawals for any reason and protocol violations) = 20%.

According to Annex 4 of the WHO document “Assessment and Monitoring of Antimalarial Drug Efficacy for the Treatment of Uncomplicated Falciparum Malaria – 2003”, a sample size of at least 175 patients would be required in each treatment group for estimating the proportion of clinical failures to within a 5 percentage point of the true value with 95% confidence.

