#### 8.2.1 Analysis for showing non-inferiority of Artekin vs AS+MQ

The primary analysis will be based on a 97.5% (one-sided) Confidence Interval (CI) computed on the difference between the 63-day PCR corrected cure rates of the test and the reference treatments, respectively.

In order to claim that Artekin is non-inferior to AS+MQ the lower limit of the CI must be  $> -0.05$  in both the modified ITT and the Per Protocol populations. The analysis on the more pure ITT population (see section 8.1) will be used for investigating robustness of results (see below).

The method for computing the CI will be specified in the SAP.

For computing the PCR-corrected cure rate, the patients who are diagnosed to be re-infected will be counted as successes (they have to be terminated on that day of follow-up) while the patients for whom the PCR is not interpretable or the sample is unavailable will be treated differently depending on the population considered (see section 8.1).

Robust analysis will be performed on the more pure ITT population by applying the following methods:

1. All patients who withdrew from the study for one of the reasons listed in section 5 (from 1 to 7) will be evaluated as failures as well as the patients for whom the PCR is not interpretable or missing
2. Patients who withdrew from the study for reasons that cannot be considered uncorrelated with the study treatments (i.e. reasons from 1 to 6) will be counted as failures (i.e. assigned with a 0 value), while the patients prematurely interrupting the study for reason

7 (lost to follow-up) will be assigned with a value ranging from 0.5 to 0.9 (imputation of a postulated probability of success for the patients for whom the treatment outcome could not be evaluated). Finally, all cured patients (or with re-infection by PCR) will be assigned with a 1 and this transformed endpoint will be summarized in terms of means and corresponding standard errors by treatment group. This analysis will be repeated for taking into account different ways of treating the patients with a non-interpretable or missing PCR (from failure to exclusion).

3. The analysis of the 63-day PCR corrected cure rates will be performed by means of the survival analysis techniques, where the non informative lost-to-follow-up patients (i.e. unable to locate the patient) and the patients with a non-interpretable or missing PCR will be censored at the time of exiting the study.

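### The 80% and 84% in section 3.4.1 are single-population powers; the power to pass in both populations, which the claim requires, is not stated and is about 75–77% by the plan's continuity-corrected method

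*Supplement*

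**What the plan says.** All references are to the amended text in the Supplement.

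- **Section 3.4.1** lists a power of 80%, a one-sided alpha of 0.025, a margin ("Non-inferiority margin for the difference (test-reference) = -0.05") and 2:1 allocation. It names the modified ITT and the PP populations together as primary.
- For the modified ITT, attrition relative to ITT and the cure rate are given as "reason number 7 of section 5) = 5%. Expected 63-day PCR corrected cure rate in this population = 93"%. For the PP population they are "rate of withdrawals for any reason and protocol violations) = 20%. Expected 63-day PCR corrected cure rate in this population = 95"%.
- The planned total is 1050, split as 700 on Artekin and 350 on AS+MQ. For the modified ITT, the section says that this size "provides a power of approximately 80% for the lower bound of a 97.5 one-sided confidence interval for the treatment difference being above -0.05"; its figure for PP is 84%. It adds that a continuity correction and unequal variances went into the power calculation.
- **Section 8.2.1** requires the lower limit to exceed -0.05 "in both the modified ITT and the Per Protocol populations". It leaves the interval method to the SAP.
- **Section 3.4.2** has the re-assessment look at withdrawals, non-evaluable PCR and the overall cure rate in each of the two primary populations. Details are left to the SAP or a separate document.

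**The concern.** When a claim needs two tests to succeed, its power cannot exceed that of the weaker test. It equals the weaker one only if every trial that passes in the modified ITT also passes in the PP population. The weaker figure here is about 80%, already at the target, so any imperfect overlap puts the power of the actual claim below the stated design power. The text prints two marginal figures and no joint one.

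At stake is the chance of missing a truly non-inferior treatment: the plan implies 20%, and its own inputs imply more. There is a possible second consequence. If the re-assessment checked power in each population separately and every assumption held, it would find about 80% and 84% and leave the sample size unchanged.

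**Working it through.** **Inputs (section 3.4.1).** Margin 0.05; z = 1.96; 700 + 350 randomised.
- Modified ITT: 5% attrition gives 700 × 0.95 = 665 and 350 × 0.95 = 332.5, with cure rate 0.93.
- PP: 20% attrition gives 560 and 280, with cure rate 0.95.
- Assumed: the same cure rate and the same attrition in both arms (true difference 0).

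**Step 1: reproduce the printed powers.** Let h = 1/nT + 1/nR and SE = √[p(1 − p)h]. With continuity correction, power = Φ[(0.05 − h/2)/SE − 1.96].
- Modified ITT: h/2 = 0.002256, SE = 0.01714; (0.05 − 0.002256)/0.01714 − 1.96 = 0.826; power 79.6%.
- PP: h/2 = 0.002679, SE = 0.01595; (0.05 − 0.002679)/0.01595 − 1.96 = 1.007; power 84.3%.

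These match the stated 80% and 84%, so the printed figures are single-population powers. Without the correction they are 83.1% and 88.0%.

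**Step 2: correlation of the two estimates.** The plan does not state it. PP patients must have the Day 63 assessment, and the modified ITT excludes only those lost to follow-up, so PP is in effect a subset. It makes up 840/997.5 = 0.842 of the modified ITT. The correlation is then 0.842 × SE(PP)/SE(mITT) = 0.842 × 0.01595/0.01714 = 0.784. The implied cure rate in the modified ITT patients outside PP is (0.95 × 0.93 − 0.80 × 0.95)/0.15 = 82%, so the inputs are mutually consistent.

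**Step 3: power to pass both (bivariate normal).**

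| Marginals (mITT, PP) | Correlation | Both pass |
|---|---|---|
| 80%, 84% (as printed) | 0.784 | 74.9% |
| 79.6%, 84.3% (reproduced) | 0.784 | 74.8% |
| 80%, 84% | 0.5 | 71.4% |
| 80%, 84% | 0.9 | 77.1% |
| 80%, 84% | 0.95 | 78.3% |
| 83.1%, 88.0% (no correction) | 0.784 | 79.3% |

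Whatever the correlation, the printed marginals bound the joint power between 0.80 + 0.84 − 1 = 64% and 80%.

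**Step 4: direct simulation.** 400,000 trials with nested populations. Per randomised patient the probabilities are: PP cured 0.76, PP failed 0.04, other modified ITT failed 0.95 × 0.07 − 0.04 = 0.0265, other modified ITT cured 0.15 − 0.0265 = 0.1235, lost 0.05.

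| Interval | mITT | PP | Both |
|---|---|---|---|
| Wald with continuity correction | 81.5% | 86.9% | 77.48% |
| Wald without correction | 85.0% | 90.5% | 82.0% |

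In both rows the joint power lies below the modified ITT power, by 4.0 and 3.0 points.

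**Scale.** By the Step 3 formula with continuity correction, 80% joint power corresponds to about 1,166 randomised patients, 11% above 1050 (116/1050). In the simulation with that correction, 1,125 patients give 80.9%.

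**The case against.** The strongest reply is that nothing printed is miscalculated. Each figure is labelled with its population, and neither is called the power of the combined rule. That stands: the gap is a missing figure, set against a stated 80% design power and a both-must-pass rule.

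A reader might infer that the trial has 75% power and is under-powered, full stop. The documents do not support that. The 75% is a normal approximation; simulating the same continuity-corrected interval gives about 77%. The correction is stated for the power calculation only, and the analysis interval is left to an SAP that is not shown. An uncorrected Wald interval gives 82% in simulation; on the same set-up Farrington–Manning and Newcombe intervals gave 84.0% and 84.7%. The cure rate assumed is also the low end of the plan's 92–95% range for the reference arm in the ITT population. So whether joint power falls below 80% depends on the interval. That it falls below the weaker marginal does not.

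A reader might also infer that the amendment dropped a joint-power calculation, because the original protocol text in section 3.4 describes a simulation of overall power. That simulation is described as covering two criteria, non-inferiority and a point estimate of at least 90%. It is not described as covering two populations, so no such step is shown to have been removed.

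Finally, section 3.4.2 can only raise the sample size and might close the gap. It does not say that power will be checked population by population, so the worry about the re-assessment is conditional. It is a reason to define the target, and does not show a fault in the re-assessment.

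**Conclusion.** The point holds in this form. The stated 80% is the power in the modified ITT alone, while the claim needs both populations. With the plan's assumptions and its continuity-corrected method, the power of the claim is about 75% by formula and 77% by simulation. That is 3 to 5 points under the target, or a 23–25% risk of missing a non-inferior treatment where the plan implies 20%. For an uncorrected Wald interval the figures are about 79% and 82%.

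The result rests on equal cure rates and attrition in the two arms, on PP being nested in the modified ITT, and on a correlation of 0.784 derived from the plan's inputs. The proportional assignment of missing PCR results in the modified ITT was not modelled. The shortfall is moderate and concerns only the chance of reaching the claim. Requiring both populations does not inflate type I error.

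**What to change.** - **Section 3.4.1:** state the power of the section 8.2.1 rule (both populations pass) beside the two marginal powers, computed for the interval the SAP adopts, with the assumed overlap of the populations. If that interval is continuity-corrected, the figure is 75–77%.
- **Section 3.4.2 and the document that details it:** define the re-assessment target as the power to pass in both populations.

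The cost is one short simulation and a stated figure that becomes slightly less favourable. The endpoint, margin, alpha and decision rule stay as they are. Because the details of the re-assessment are to be finalised before any interim analysis, both changes can be made in time for it.
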